### Participant protections and ethics

The protocol adheres to the latest revision of the Helsinki Declaration and the Chinese law of human study and has been approved by the Research Ethical Committee of Yichang Hospital of Traditional Chinese Medicine, Clinical Medical College of Traditional Chinese Medicine, China Three Gorges University. The participants are informed of the potential benefits, risks, alternatives, and responsibilities during the study before they are asked to provide consent. Potential mild adverse events, reported to be related to electro-acupuncture treatment, are pain, bleeding, tiredness, and a feeling of faintness in the acupuncture group [23], and skin redness and pressure marks in the other groups, but these mild symptoms will generally resolve spontaneously after treatment. Additionally, ABVN is thought to be involved in some peculiar somatovisceral reflexes. For instance, an ear-cough reflex (Arnold’s reflex) is estimated to be present in approximately 4% [24] of the general population, while there is rare occurrence of ear-gag reflex, ear-lacrimal reflex and auricular syncope [24,25]. So there is a rare possibility that patients in the two groups receiving ABVN stimulation might have these reflexes. Participants who show any adverse effects during the course of the therapy will receive appropriate treatment immediately. All adverse effects will be documented, and patients with persistent worsening symptoms will be withdrawn from the study.

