### Primary outcome measures

The primary outcome is evaluated using the Tinnitus Handicap Inventory, which evaluates 25 items grouped into a functional subscale (11 factors), an emotional subscale (9 factors), and a catastrophic subscale (5 factors). Each question of the Tinnitus Handicap Inventory can be answered by either ‘often’ (4 points), ‘sometimes’ (2 points), or ‘never’ (0 points). The total score allows the tinnitus to be categorized as: ‘slight’ (0 to 16 points), ‘mild’ (18 to 36 points), ‘moderate’ (38 to 56 points), ‘severe’ (58 to 76 points), or ‘catastrophic’ (78 to 100 points). The assessment is at baseline (before randomization), and in the 4th and 8th week, with further follow-up visits after termination of the treatment at the 12th week.

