### Statistical methods

The trial aims to detect a difference between the four study groups. We present here our power analysis for the primary outcome only. This is deemed a clinically significant difference of a 20-point or greater reduction in score on the Tinnitus Handicap Inventory following treatments. Since this is a novel therapy, we used data from a previous proof-of-concept feasibility study [21], the mean decrease rate is 28% in the VNS group and 0.97% in the control group.

The following formula was used for a four-group trial [22]:$$ {n}_1={n}_2=\frac{{\left({\mu}_{\alpha }+{\mu}_{\beta}\right)}^22P\left(1-P\right)}{{\left({P}_1-{P}_2\right)}^2} $$

Calculations are performed using 80% power and a 5% significance level (two-side). The required sample size is approximately 27 participants for each group. Assuming a 10% dropout rate, we plan to enroll a total of 120 participants with four groups of equal size (30 participants per group).

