### Statistical analysis

In this trial, our primary outcome measure is the Tinnitus Handicap Inventory. We define the treatment response as a reduction in score on the Tinnitus Handicap Inventory following treatments of 20 points or more. First, baseline characteristics will be analyzed using descriptive statistics for each group. Then repeated measures analysis is performed to make comparisons among the treatment groups and the control group (ABVN plus tone versus electrical acupuncture, non-ABVN plus tone versus electrical acupuncture, and ABVN versus electrical acupuncture) at different time points (4th, 8th, and 12th week). If a significant difference is found, the next step is to make comparisons among the three treatment groups in effectiveness. Multiple comparisons will be adjusted according to the Bonferroni correction method. The Kruskal-Wallis test will be employed in the analysis of skewed distribution data. Analysis of variance will be used for numerical variables, and the *χ*^2^ test for categorical variables.

Statistical analysis will be performed by the Medical College of China Three Gorges University, [name]. The statistician is blinded from the allocation of groups. The SPSS 15.0 software package (SPSS Inc., Chicago, IL, USA) will be used to analyze the data.

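### The withdrawal rule for worsening patients does not separate stopping treatment from ending follow-up, so outcome data may be lost selectively and unequally between arms

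*Protocol article*

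**What the plan says.** The rule stands in the protocol article, section Participant protections and ethics, in the sentence that requires adverse effects to be documented: "patients with persistent worsening symptoms will be withdrawn from the study". Earlier in that section the same noun clearly refers to adverse events: "these mild symptoms will generally resolve spontaneously after treatment". The section does not define persistent or worsening.

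Under Statistical analysis, "our primary outcome measure is the Tinnitus Handicap Inventory", and response is "a reduction in score on the Tinnitus Handicap Inventory following treatments of 20 points or more". After baseline, THI is assessed "in the 4th and 8th week, with further follow-up visits after termination of the treatment at the 12th week" (Primary outcome measures). The secondary scales follow the same schedule.

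For the comparison of arms the article says: "Then repeated measures analysis is performed to make comparisons among the treatment groups and the control group". Electrical acupuncture is the control in all three of these contrasts. On loss of patients, Statistical methods says: "Assuming a 10% dropout rate, we plan to enroll a total of 120 participants".

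**The concern.** The rule removes patients from the study, where a rule about treatment alone would have left their outcome data intact. Taken literally, a patient withdrawn under it gives no further questionnaires and no further safety follow-up. The trigger arises after randomisation and is tied to the treatment received. The patients left at weeks 8 and 12 are then a selected subset, and the selection can differ by arm.

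If the trigger covers worsening tinnitus, an arm that makes more patients worse sheds its poor results and looks better than it is. If it covers only adverse effects, the link to THI is weaker. The loss still depends on arm, because the same section expects pain, bleeding, tiredness and faintness with acupuncture, skin redness and pressure marks in the other groups, and vagal reflexes only in the two groups stimulated at the auricular branch. Selective loss in the acupuncture arm would affect all three first-stage contrasts.

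An analysis plan can choose the analysis set and the model. It cannot supply scores that the conduct rule stopped anyone from collecting.

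**Working it through.** **1. The plan's own figure.** The formula in Statistical methods, with the rates 28% and 0.97% and P = (0.28 + 0.0097)/2 = 0.14485, gives

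n = (1.960 + 0.842)² × 2 × 0.14485 × 0.85515 / (0.28 − 0.0097)² = 26.6, so 27 per group.

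Then 27/0.90 = 30 per group and 4 × 30 = 120. The stated size reproduces and is not at fault. The allowance amounts to 3 of 30 patients per arm, for all causes of loss together.

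**2. Upper bound on the shift in one arm.** Assumptions: THI improvement is normal, and exactly the worst fraction q of the arm is removed. The mean improvement of those left then rises by φ(z_q)/(1 − q) SD. The article gives no SD of THI change, so a range of 15 to 25 points is assumed. It gives no withdrawal counts either, so 1 to 6 of 30 are shown. Points are computed from unrounded shifts.

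| Lost of 30 | q | Shift (SD) | Points, SD 15 to 25 |
|---|---|---|---|
| 1 | 0.033 | 0.08 | 1.2 to 1.9 |
| 2 | 0.067 | 0.14 | 2.1 to 3.5 |
| 3 | 0.100 | 0.20 | 2.9 to 4.9 |
| 6 | 0.200 | 0.35 | 5.2 to 8.7 |

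**3. Responder scale.** Take a true rate of 28% for illustration, that is 0.28 × 30 = 8.4 expected responders. Removing 3 worsening non-responders gives 8.4/27 = 31.1%. Removing 6 gives 8.4/24 = 35.0%.

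**4. Between arms, no true difference.** This is a simulation of 40,000 trials with 30 patients per arm, the worst patients removed, and a t test on those left. The Bonferroni level is 5%/3 = 1.67%, for the three first-stage contrasts.

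| Losses | False difference (SD) | Type I error at 5% | Type I error at 1.67% |
|---|---|---|---|
| 0 v 0 | 0 | 4.8% | 1.7% |
| 1 v 0 | 0.07 | 6.3% | 2.3% |
| 2 v 0 | 0.13 | 9.2% | 3.7% |
| 3 v 0 | 0.19 | 12.4% | 5.6% |
| 6 v 0 | 0.34 | 28.0% | 15.5% |
| 3 v 3 | 0 | 8.2% | 3.3% |

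With equal losses the difference is unbiased on average. The type I error still rises, because trimming shrinks the observed spread.

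**5. What analysis could recover.** Suppose withdrawal depends on an earlier THI value that was recorded, with an assumed correlation of 0.6 between visits and 10% lost. Analysing completers only gives a bias of 0.6 × 0.195 = 0.12 SD. Using the earlier visit to predict the later one, as a likelihood-based model would, brings the simulated bias to about 0.

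**The case against.** The strongest reply is that the clause belongs to a passage on adverse effects, where symptoms has just been used for needle and skin reactions. On that reading nobody is removed for a poor THI course, the patients removed need not be the worst on THI, and the formula in step 2 does not apply to them. The section also calls the expected events mild or rare. Its only frequency, about 4% for the ear-cough reflex, is a population prevalence of a reflex and gives no withdrawal rate. Spending the whole 10% allowance on this one cause is therefore not supported. These points stand, and they limit the size of the problem. They do not remove it, because loss that depends on treatment and differs by arm remains.

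A second reply is that handling after withdrawal, analysis sets and missing data are commonly left to a fuller document. That is fair for the analysis, and no omission is charged here. The withdrawal rule itself, however, is stated in the article and needs correcting there.

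A reader might infer that the trial deletes its worst THI results by design and that no analysis could repair this. The article does not say so. The THI reading is one of two, non-collection follows from the plain wording but is not spelled out, and scores from visits already attended could be used. The method is named only as repeated measures, which neither commits to a likelihood-based model nor rules one out. Nor does the article state that safety follow-up is cut short: it says that adverse effects are documented and treated. The gap is that withdrawal from the study, taken literally, would end it.

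**Conclusion.** The point holds as a badly worded conduct rule. Followed literally, it ends outcome and safety follow-up for a treatment-related subset of randomised patients, probably unequally across arms, and enlarging the sample does not address that.

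The size cannot be determined from the article. The figures of 0.20 SD for 3 of 30 and 0.35 SD for 6 of 30 (about 3 to 5 and 5 to 9 THI points) are ceilings. They rest on normality, on removal of exactly the worst THI patients, and on an assumed SD of 15 to 25. They carry over to a contrast between arms only when losses differ. If the rule concerns adverse effects alone, the bias in THI could be much smaller and its direction is unknown. If worsening was recorded at an earlier visit and all visits are modelled, most of the bias goes. Patients withdrawn before week 4 would have only baseline data to contribute.

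**What to change.** Reword the sentence under Participant protections and ethics so that it does three things:

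- say whether symptoms means tinnitus, adverse effects or both;
- separate stopping treatment from leaving the study;
- state that the week 4, 8 and 12 questionnaires and adverse-event follow-up continue after treatment stops, unless the patient withdraws consent.

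Under Statistical analysis, add that all randomised patients are analysed in their allocated group using all available visits.

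The cost is a short wording change and a few extra questionnaires. The article reports that recruitment is under way, so an early change limits how many patients are lost under the present wording. When treatment should stop is a clinical decision; it is not judged here and the rewording leaves it unchanged.

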## Discussion

We have presented the design and protocol for the randomized controlled clinical study for tinnitus patients. If it proves successful, this new treatment method could offer hope to millions of patients who are affected by tinnitus.

Although the exact pathophysiology of tinnitus still remains elusive, it is believed that an abnormal balance between inhibition and excitation causing map reorganization of central auditory circuits underlies many forms of tinnitus [26]. Moreover, signs of abnormal activity were not only revealed in the central auditory system but also in non-auditory areas, including the limbic system [27-29]. The annoyance of tinnitus is not correlated with its acoustic characteristics, but there is a significant correlation with psychological symptoms [30]. The autonomic nervous system is a major factor in the difference between simply perceiving tinnitus and being distressed by it [31]. Studies have reported that tinnitus distress correlated positively with sympathetic markers and negatively with parasympathetic markers [32,33]. Accumulating evidence illustrates that tinnitus is correlated with symptoms of distress, such as emotional stress and depression for the important role of the limbic system in the pathophysiology of tinnitus, which is based on the further understanding of auditory-limbic interactions [34-36].

Vagal nerve stimulation was developed based on this growing understanding of tinnitus. It may work by activating the nucleus of the solitary tract, which, in turn, may activate the locus coeruleus and nucleus basalis, which release neuromodulators that have significant effects on learning and memory and in plasticity regulation by modulating neurons in the cortex, hippocampus, and amygdala [26]. Engineer and colleagues [8] have indicated that cervical VNS paired with specific auditory stimuli completely eliminated the physiological and behavioral correlates of the phantom sound. They observed that pairing tones with VNS significantly acutely increased excitability and suppressed spontaneous multi-unit activity in rat auditory cortex [37]. Indeed, beneficial effects in relieving psychological symptoms have been confirmed in patients with tinnitus using invasive VNS pairing tones [21] or transcutaneous VNS paired with tones [19,38] in recent small sample pilot studies. However, another experiment also demonstrated that VNS-directed long-lasting reversal of pathological neural plasticity is driven by the repeated association of VNS with tones, and not by VNS alone [8]. German researchers [14] claimed that no clinically relevant improvement of tinnitus complaints was observed after transcutaneous VNS alone. To some extent, this may confirm the suggestion that stimulation at ABVN might prove less effective than VNS because fibers from the auricular branch do not primarily target the nucleus of the solitary tract and so only target it partly. Otherwise, as these researchers themselves suggested [14], the most probable explanation is that VNS alone is not effective in reducing tinnitus, which is supported by the work of Engineer *et al*. [8]. While sound stimulus alone, as a common sensory exposure treatment strategy, has been applied to treat tinnitus for many years [39,40], studies have indicated that it has only provided some temporary relief [41,42]. Therefore, to identify whether ABVN or the combination of ABVN and sound stimulus plays a more important role in relieving tinnitus, we designed this four-armed novel trial to determine their specific effect on tinnitus.

Acupuncture is an important part of traditional Chinese medicine. It has been accepted in China for thousands of years and is now used as an alternative and complementary medical therapy in Western countries. Meta-analysis results have indicated that acupuncture or acupuncture combined with other therapies is superior to medication alone or non-acupuncture treatments in treating subjective tinnitus [43]. However, in another systematic review, acupuncture for the treatment of tinnitus has not been demonstrated to be efficacious [44]. Whether acupuncture is effective or not in the treatment of tinnitus is a question worthy of discussion. According to the theory of traditional Chinese medicine, the shaoyang meridians of the hand and foot travel to the ear region, so acupoints of the shaoyang meridians located both in local and distant areas of the ear are used to treat tinnitus in this protocol. In addition, the specific acupoints Yifeng (TE17), Tinghui (GB2), Xiaxi (GB43), and Zhongzhu (TE3) are usually chosen in treating tinnitus.

Auricular acupuncture, as an important branch of acupuncture, has also been utilized in the treatment of diseases for years. In ancient China’s earliest medical text *Huang Di Nei Jing*, which was compiled in the 5th century BC, the correlation between the external ear and the body or viscera is described. In 1957, [name], a physician in France, first originated the concept of an inverted fetus map on the external ear [45]. He proposed a theory that there is a somatotopic and viscerotopic representation on the auricle [46]. According to these theories, disorders from a particular part of the body or viscera can be treated by the corresponding points in the ear [46,47]. Therefore, related auricular acupoints such as Kidney (CO10), Yidan (CO11), or Liver (CO12) are usually selected to treat tinnitus, which, according to the organ-viscera theory of traditional Chinese medicine, results from insufficient Kidney qi or dampness-heat of the Liver and Gallbladder. The Shenmen point (TF4) has the effect of tranquilizing the mind [48,49]. It is often utilized to remedy mental illnesses or psychiatric disorders, such as insomnia [50], anxiety [51,52], or tinnitus [53]. However, the physiological mechanisms associated with these auricular acupoints remain unclear. In this study, it is proposed that the autonomic and the central nervous system could be modified by auricular vagal stimulation via projection from the ABVN to the nucleus of the solitary tract [54], which might work through the neuromodulator system, thus directing plasticity to treat tinnitus.

However, our study has several potential limitations. First, all the outcome measures are self-assessments instead of objective measures. To some extent, objective measures carry out relatively convincing evidence. However, the Tinnitus Handicap Inventory [55,56], visual analogue scale [56], and Hospital Anxiety and Depression Scale [57] have been much used in most of the randomized controlled trials on tinnitus and they are proved to be efficient in reflecting the subjective emotional changes related to tinnitus. Second, this trial is single-blind, therefore, the subjective factors from therapists might bias the outcome assessments. However, it is hard to blind the therapists, who are required to be familiar with treatments for the specific grouping assignment. Another limitation concerns the fact that this is a single center study. It does not lend results to great generalizability to more diverse sets of patients in more diverse regions. In addition, the sample size in this study is relatively small. A large sample, multicenter, and objective measures to assess the effectiveness of treatment should be included in a future study.

## Trial status

This trial is currently recruiting participants.

### Consent

Written informed consent was obtained from the participants for publication of this manuscript and accompanying images. A copy of the written consent is available for review by the editor-in-chief of this journal.

## Abbreviations

ABVN: Auricular branch of vagus nerve
VNS: Vagus nerve stimulation
